### 2.3. Study Protocol

Patients who meet the inclusion criteria will be invited to participate in the study and will be asked to sign the informed consent. All patients must have a coproparasitological study, a *Strongyloides* specific culture, and a *S. stercoralis* serology performed at baseline. The initial evaluation will include: Full blood cell count, basic biochemistry (glucose, kidney function, and liver profile), HIV serology, and detection of microfilaria in peripheral blood to screen for loiasis in patients coming from endemic areas. In addition, a serum sample (for sample repository), a fresh stool sample (for sample repository and *S. stercoralis* PCR), and a plasma sample (for pre-dose ivermectin population PK) will be collected and stored at −80 °C. At the time of inclusion, the time of post-dose peripheral blood (plasma sample) extraction for the ivermectin population PK will be randomly assigned to 8 different points: 1.5, 3, 4, 5, 6.5, 24, 48, and 72 h after treatment (see Table 1).

Patients will be treated with 200 mcg/kg ivermectin (3 mg tablets, Exeltis Laboratory, Madrid, Spain) in a single dose: <50 kg (9 mg), 50–64.9 kg (12 mg), 65–79.9 kg (15 mg), 80–94.9 kg (18 mg), >95 kg (21 mg). Treatment will be directly observed at the hospital or by videocall. Forty-eight hours after the administration of the drug, investigators attempt make a phone call to inquire about possible adverse events using a structured questionnaire. In case of presenting relevant adverse events, the patient could be referred for clinical and analytical evaluation (at treating physician discretion). Follow-up visits will take place 3 and 6 months after treatment and will include the following assessments: Hemogram, *S. stercoralis* serology, coproparasitological study and *Strongyloides* specific culture (in case they were positive at baseline). In addition, a serum sample (for sample repository) and a fresh stool sample (for sample repository and *S. stercoralis* PCR determination) will be collected and stored at −80 °C at both visits. 

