## 1. Introduction

Human strongyloidiasis caused by the nematode *Strongyloides stercoralis* affects an estimated 600 million people worldwide, especially in tropical and subtropical areas [1]. Until now, scarce efforts have been made to reduce its prevalence. However, the World Health Organization has recently included strongyloidiasis among the targets for 2030 soil-transmitted helminth (STH) control [2]. 

Most of the patients with *S. stercoralis* infection are asymptomatic or present with mild symptoms in the form of gastrointestinal disturbances (abdominal pain, diarrhea, vomiting), respiratory symptoms (cough, dyspnea), and skin lesions (rash, larva currens) [3]. This parasite can persist in the host indefinitely in the absence of reinfections thanks to its ability to autoinfect the human host. Under immunosuppressive conditions such as corticosteroid therapy, solid organ transplantation, or human T lymphotropic virus 1 (HTLV-1) infection, its cycle of autoinfection can be amplified, leading to severe clinical presentations with high mortality, such as *Strongyloides* hyperinfection syndrome and disseminated strongyloidiasis [4,5]. 

Autochthonous cases of trongyloidiasis in Western European countries have been described, although they are currently anecdotal, restricted to specific areas, and mostly affecting elderly males who worked in agriculture in the past [6,7,8]. However, due to migratory flows and the increase in international travels in recent decades, strongyloidiasis is increasingly diagnosed outside endemic areas [9]. A recent review of the literature showed a prevalence of *S. stercoralis* infection ranging from 10% to 20% in immigrant population living in Spain. These data support the active screening of populations coming from endemic areas given the potential risk of serious presentation in situations of immunosuppression [10]. The frequency of this parasitosis and its potentially deleterious consequences has led the European Center for Disease Control to include strongyloidiasis in the routine screening of migrants coming from endemic areas [11].

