### 2.2. Outcomes

The primary outcome will be noninferiority of the cure rate of immunosuppressed patients compared to immunocompetent patients. Cure rate is defined as the proportion of patients with a negative direct parasitological test and negative *S. stercoralis* serology or decrease of at least 50% of OD index at 6 months after treatment administration. We used a noninferiority margin of 14% to assess the primary outcome (i.e., lower bound of the 1-sided 95% CI of the difference between cure rates in immunosuppressed versus immunocompetent patients was no more than –14%). The secondary objective will be to compare the safety and tolerability of single dose ivermectin for the treatment of uncomplicated strongyloidiasis between immunosuppressed and immunocompetent patients. Three sub-studies have been prespecified: Evaluation of the usefulness of *S. stercoralis* PCR in feces in the follow-up after treatment of uncomplicated strongyloidiasis in adult patients (proportion of patients with negative *S. stercoralis* PCR after treatment compared to proportion of patients that fulfill the cure criteria),Determination of the population pharmacokinetics (PK) of ivermectin in a single dose for the treatment of uncomplicated strongyloidiasis in adult patients, andCreation of a repository of serum and stool samples from adult patients (immunosuppressed and immunocompetent) with uncomplicated strongyloidiasis (samples before and after treatment with ivermectin) for later use in the evaluation of new diagnostic tools or biomarkers.

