## Figures and Tables

**Table 1 pathogens-10-00812-t001:** Visit schedule.

	Screening Period (from −30 Days to Day 0)	Day 0	Population PK Day	Day 2 (Telephone Visit)	Month 3	Month 6
Informed consent	X					
Demographic and clinical information	X					
Concomitant medication	X	X	X	X		
Directed anamnesis	X	X	X	X	X	X
Physical examination	X	X	X		X	X
Ivermectin treatment		X				
Adverse events		X		X		
Full blood cell count	X			X ^a^	X	X
Biochemistry	X			X ^a^		
HIV serology	X					
*Loa loa* screening	X ^b^					
Coproparasitological study	X				X ^c^	X ^c^
Agar plate culture	X				X ^c^	X ^c^
*S. stercoralis* serology	X				X	X
*S. stercoralis* PCR	X				X	X
Serum and stool samples for repository		X			X	X
Plasma sample for PK		X	X			

^a^ In case of presenting relevant adverse events (at treating physician discretion). ^b^ In patients coming from endemic areas for *Loa loa*. ^c^ Only when they were positive at baseline.

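### Adverse events and concomitant medication are not scheduled at months 3 and 6, and cure rests on month-6 tests alone, so a re-treated patient can be classified as a single-dose cure

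*Protocol article*

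**What the plan says.** **Safety recording.** Section 2.3 describes a single attempted contact: "Forty-eight hours after the administration of the drug, investigators attempt make a phone call to inquire about possible adverse events using a structured questionnaire". Its list of assessments for the 3- and 6-month visits covers blood count, serology, stool study and culture (the last two only if positive at baseline) and stored samples. Adverse events and medication are not in that list.

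**Table 1.** The adverse-event row, "Adverse events X X", has its marks at Day 0 and the Day 2 call. The medication row, "Concomitant medication X X X X", has its marks at screening, Day 0, the PK day and Day 2. Both rows are blank at months 3 and 6. The PK day is one of "1.5, 3, 4, 5, 6.5, 24, 48, and 72 h after treatment", so medication can be recorded up to 72 h in some patients. Directed anamnesis and physical examination are marked at months 3 and 6.

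**Endpoint.** Section 2.2 defines cure as "negative direct parasitological test and negative *S. stercoralis* serology or decrease of at least 50% of OD index at 6 months after treatment administration". No condition is placed on what happened between Day 0 and month 6. Section 2.1 names hyperinfection, dissemination and ivermectin in the previous year, but only as exclusions at entry.

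**Safety objective.** Section 2.2 makes the comparison of safety and tolerability between the two groups the secondary objective.

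**The concern.** The study asks whether one dose is as effective in immunosuppressed (IS) as in immunocompetent (IC) patients. Serology is repeated in everyone at month 3, and direct tests in those positive at baseline, all in each site's routine laboratory. Persistent infection can therefore come to light three months before the endpoint. If more antiparasitic treatment follows and the month-6 tests meet the definition, that success is credited to the single dose, and the schedule provides no medication entry that would reveal it.

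The bias runs towards noninferiority. If single-dose cure is lower in the IS group, that group has more failures to convert, so even equal re-treatment rates narrow the observed difference. If re-treatment is more common in IS patients, the effect is larger. The Introduction gives a reason to expect this, since it describes amplified autoinfection under immunosuppression as "leading to severe clinical presentations with high mortality".

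Safety has a parallel gap. Hyperinfection or dissemination after Day 2 is the harm that the Introduction singles out, yet it has no scheduled adverse-event entry and no role in the outcome.

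**Working it through.** **1. The passages side by side**

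| Item | Day 0 to Day 2 / PK day | Month 3 | Month 6 |
|---|---|---|---|
| Adverse events | Day 0, Day 2 | blank | blank |
| Concomitant medication | Day 0, PK day, Day 2 | blank | blank |
| Directed anamnesis | marked | marked | marked |
| Serology | – | marked | marked (endpoint) |
| Stool study, culture | – | if positive at baseline | if positive at baseline (endpoint) |

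Text and table agree, so the blanks are the schedule as stated and not a lost table mark. Directed anamnesis is marked at Day 0 and Day 2 alongside separate marks for adverse events and medication, so the table treats them as different items.

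**2. The plan's own sample size**

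Inputs from section 2.6: IC cure 85%, margin 14 points, one-sided α 5%, power 80%, 10% non-evaluable. Assumption: IS cure is also 85%, since only the IC rate is stated.

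n = (1.645 + 0.842)² × 2 × 0.85 × 0.15 / 0.14² = 80.4, rounded up to 81 evaluable per group. 81 / 0.9 = 90 per group, 180 in total. This matches the plan.

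**3. Effect of uncounted re-treatment**

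Put the true single-dose difference at the margin: IS 71%, IC 85%. Let *r* be the share of single-dose failures who are re-treated and, by assumption, all meet the cure definition at month 6.

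- Observed IS cure = 0.71 + 0.29*r*
- Observed IC cure = 0.85 + 0.15*r* (same *r* in both groups), or 0.85 (IS only)
- SE = √[p_IS(1 − p_IS)/81 + p_IC(1 − p_IC)/81]
- P(noninferiority declared) = Φ[(0.14 + p_IS − p_IC)/SE − 1.645]

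With *r* = 0 the numerator is 0 and the result is Φ(−1.645) = 5.0%, the nominal rate.

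Example, *r* = 0.2 in both groups: p_IS = 0.768, p_IC = 0.880, SE = 0.0592. (0.14 − 0.112)/0.0592 = 0.473, and Φ(0.473 − 1.645) = 12.1%.

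Example, *r* = 0.2 in IS only: p_IS = 0.768, p_IC = 0.850, SE = 0.0614. (0.14 − 0.082)/0.0614 = 0.944, and Φ(0.944 − 1.645) = 24.2%.

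| *r* | Observed IS | Observed IC (both) | False noninferiority, both groups | False noninferiority, IS only |
|---|---|---|---|---|
| 0 | 71.0% | 85.0% | 5.0% | 5.0% |
| 0.1 | 73.9% | 86.5% | 7.8% | 11.8% |
| 0.2 | 76.8% | 88.0% | 12.1% | 24.2% |
| 0.3 | 79.7% | 89.5% | 18.5% | 42.5% |

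**4. Sensitivity to the conversion assumption**

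If only 85% of re-treated failures meet the definition at month 6 (also an assumption), replace *r* by 0.85*r*. The figures become 7.3%, 10.6% and 15.3% for both groups, and 10.5%, 19.8% and 33.6% for IS only.

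**5. In patients rather than rates**

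One IS patient in 81 is 1.23 points. At the margin, with IC unchanged, two misclassified IS patients raise false noninferiority to about 10.5%, and four to about 20%.

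**The case against.** The strongest reply is that this is a journal article. How re-treatment or death before the endpoint is classified is often left to a full protocol or analysis plan, and section 2.2 never says that re-treated patients count as cured. That is fair, and a reader should not infer that the investigators intend to count them so. But the definition in section 2.2 is complete as it stands and looks only at month-6 tests, and Table 1 fixes which visits record what. An analysis plan can add a failure rule, but it cannot apply one to medication data that the schedule does not collect.

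Second, months 3 and 6 are not unobserved. Directed anamnesis, physical examination and blood count take place, and the content of the anamnesis is not defined, so it may bring re-treatment or complicated disease to light. This stands, and rules out saying that such cases must be missed. Nothing, however, links those items to the adverse-event record or to the cure definition.

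Third, the re-treatment pathway has no numbers behind it. The article sets no month-3 failure criterion and gives no re-treatment frequency. A patient positive only by serology has just a month-3 optical density value to prompt action, and a re-treated patient must still meet the serological criterion by month 6. All this stands, so the magnitude is illustrative. More frequent re-treatment in IS patients is plausible but undocumented, which is why the equal-rate figures are given alongside.

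Two further readings go too far. It is tempting to say that a patient who dies of hyperinfection could count as cured. Such a patient has no month-6 negative test, so the misclassification route applies only to survivors treated to negativity. Nor does medication recording stop at 48 h for everyone: with a 72 h PK sample it extends to 72 h.

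**Conclusion.** The point holds as a defect in the recording schedule and the endpoint rule. The stated plan permits a re-treated patient, or a survivor of complicated strongyloidiasis treated to negativity, to be classified as a single-dose cure. It also leaves complicated disease after Day 2 without a scheduled place in the safety comparison. The bias favours noninferiority even when re-treatment is equally common in both groups.

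The size cannot be established from the article. The results in the working rest on a true difference exactly at the margin, 81 evaluable per group, a normal approximation with unpooled variance, and assumed re-treatment and conversion rates. They show that a handful of patients is enough to matter, not that the trial will be biased by a given amount. The correction should be made: it is cheap, and the information may not be reliably recoverable afterwards.

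**What to change.** 1. In Table 1, mark concomitant medication (specifying antiparasitic drugs and changes in immunosuppression) and adverse events at months 3 and 6, and add both to the list of follow-up assessments in section 2.3.
2. In section 2.2, state that, for analysis, any further anti-Strongyloides treatment, hyperinfection or dissemination, or strongyloidiasis-related death before the month-6 assessment is classified as not cured.

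This changes recording and outcome classification only. It sets no rule on who should be treated, when or how, and the sample size calculation is unaffected. The cost is four marks in the table, a short form at visits that already take place, and one sentence. The drawback is that the reported cure rate may be slightly lower.

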### 2.4. Microbiological and Immunological Techniques

Coproparasitological studies, agar plate culture, and *S. stercoralis* serology will be performed in each participant site using their routine techniques. Stool microscopic examination will be performed using one of the following concentration techniques: The Ritchie’s formalin-ether technique, the commercial device Midi and Mini Parasep^®^ (APACOR Ltd., Wokingham, UK), or the commercial device REAL Mini System^®^ (Durviz SL, Paterna, Spain). The specific fecal culture for *S. stercoralis* larvae will be performed using the agar plate or charcoal techniques. Detection of serum anti-*S. stercoralis* IgG will be performed through different enzyme-linked immunosorbent assay (ELISA)-based commercial kits depending on the center: SciMedx *Strongyloides* serology microwell ELISA (SciMedx Corporation, Denville, NJ, USA), NovaLisa *Strongyloides* (NovaTec Immunodiagnostica GmbH, Dietzenbach, Germany), *Strongyloides* IgG IVD-ELISA (DRG Instruments GmbH, Marburg, Germany), ELISA from Bordier (*Strongyloides ratti*; Bordier Affinity Products SA, Crissier, Switzerland), Euroimmun anti-*Strongyloides* ELISA IgG (*Strongyloides papillosus;* Euroimmun AG, Luebeck, Germany). 

Molecular detection of S. stercoralis will be performed at the Parasitology Reference and Research Laboratory of the National Microbiology Center of the Carlos III Health Institute. Genus-specific primers targeting the small subunit ribosomal RNA (SSU rRNA) gene of *Strongyloides* spp. will be used to detect the presence of the parasite in a qualitative real-time PCR (qPCR) assay using SybrGreen reagents (Invitrogen, San Diego CA, USA) as described elsewhere [15].

### 2.5. Ivermectin Population Pharmacokinetics

The technique for quantifying ivermectin concentrations in plasma will be performed by liquid chromatography coupled to electrospray ionization mass spectrophotometry. In this case, a simple liquid-liquid extraction will be made with deuterated ivermectin as an internal standard to normalize the variations in the processing method, and to detect free ivermectin in plasma in a specific way and quantify its concentrations using a standard line. To ensure that it complies with the requirements established by the EMA and FDA for bio-analytical methods, a validation of the ivermectin processing and determination methods will be carried out using an Acquity chromatography system coupled to a Xevo-TQ massas detector (Waters^®^, Milford, MA, USA). Finally, to date, the long-term stability studies for ivermectin detection in plasma samples that have been carried out have shown a stability of 12 months at −20 °C [16]. For this study, we plan to collect the samples, store them, and analyze them within 24 months. For this reason, together with the validation, a long-term stability study will be carried out to cover the range of 12 to 24 months.

### 2.6. Sample Size Calculation and Statistical Analysis

Assuming a response rate of 85% in the immunocompetent group, a 1-sided α value of 5%, a power of 80%, and a maximum of 10% non-evaluable subjects to show noninferiority at a margin of 14%, we estimated the sample size at 180 assessable subjects per group (90 patients in the IS group and 90 patients in the IC group). Inclusion will be performed competitively among all centers.

Categorical data will be presented as absolute numbers and proportions, and continuous variables will be expressed as means and standard deviations (when normal distribution is demonstrated using the Kolmogorov-Smirnov test) or as medians and interquartile ranges. The χ^2^ test or Fisher exact test, when appropriate, will be used to compare the distribution of categorical variables, and the Student’s *t* test or Mann–Whitney U test will be used for continuous variables. Results will be considered statistically significant if the *p* value is <0.05. SPSS software for Windows (Version 19.0; SPSS Inc, Chicago, IL, USA) will be used for statistical analyses. 

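### The sample-size sentence labels 180 as assessable patients per group, but on its own inputs 180 is the total to enrol and 81 per group must be assessable

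*Protocol article*

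**What the plan says.** Section 2.6 (Sample Size Calculation and Statistical Analysis) lists the inputs and the result in one sentence. The inputs are:

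- control cure rate: "Assuming a response rate of 85% in the immunocompetent group"
- significance level: "a 1-sided α value of 5"%
- power: 80%
- loss: "a maximum of 10% non-evaluable subjects"
- margin: "to show noninferiority at a margin of 14"%

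The result is: "we estimated the sample size at 180 assessable subjects per group (90 patients in the IS group and 90 patients in the IC group").

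Section 2.2 (Outcomes) uses the same margin and a one-sided 95% confidence bound, so the design inputs agree between the two sections. No other part of the article gives a sample size. Section 2.6 does not state the cure rate assumed for the immunosuppressed (IS) group.

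**The concern.** Two labels on the number 180 look wrong.

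- **Per group.** The bracket gives "90 patients in the IS group and 90 patients in the IC group", which makes 180 the sum of the two groups. The sentence disagrees with itself by a factor of two.
- **Assessable.** The 10% non-evaluable allowance is one of the inputs. A figure that already includes it counts patients to enrol, not patients with an evaluable outcome.

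This figure is both the recruitment target and the basis of the power for the primary noninferiority comparison. Inclusion is competitive across eight sites, so recruitment ends at one shared count. The outcome is assessed six months after treatment, so enrolled and assessable patients will be different counts. A reader who takes the sentence literally could aim for 180 per group, or wait for 180 assessable patients. The number that the 80% power needs appears nowhere in the article.

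**Working it through.** **Inputs.** From section 2.6: control cure rate 0.85, one-sided alpha 0.05 (z = 1.645), power 0.80 (z = 0.842), margin 0.14, non-evaluable 10%, equal groups. One input is assumed: a true IS cure rate of 0.85, so that the true difference is zero. The article's Discussion supports this, since it reports that efficacy seems the same in both groups when disease is not severe.

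**Step 1. Reproduce the plan's figure.** Unpooled normal approximation for noninferiority of two proportions:

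n per group = (1.645 + 0.842)² × 2 × 0.85 × 0.15 / 0.14² = 80.4, rounded up to **81 assessable**.

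Allowing for 10% non-evaluable: 81 / 0.9 = **90 enrolled per group**, and 2 × 90 = **180 enrolled in total**. Assessable in total: 2 × 81 = 162.

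The bracketed 90 and 90 are reproduced exactly, as enrolment figures.

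**Step 2. Power under each reading.** Power = Φ(0.14 / √(2 × 0.85 × 0.15 / n) − 1.645), where n is the number assessable per group. The last column enumerates all outcomes of two binomials, using the Wald bound.

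| Assessable per group | 0.14 / SE | Power, normal approximation | Power, exact enumeration | Enrolment needed at 10% loss |
|---|---|---|---|---|
| 81 | 2.495 | 80.2% | 80.2% | 90 per group, 180 in total |
| 90 | 2.630 | 83.8% | 83.5% | 100 per group, 200 in total |
| 180 | 3.720 | 98.1% | 98.0% | 200 per group, 400 in total |

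Only the first row matches the stated 80% power.

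**Step 3. Could another method give 180 assessable per group?** Other choices with equal cure rates, and two-group superiority formulas for 85% against 71%, were tried:

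| Variant | Assessable per group | After 10% inflation |
|---|---|---|
| One-sided alpha 2.5% | 103 | 115 |
| 90% power | 112 | – |
| 90% power, one-sided alpha 2.5% | 137 | – |
| Continuity correction | about 95 | about 105 |
| Farrington–Manning variance | about 85 | about 95 |
| Two-sided superiority, 85% vs 71%, continuity-corrected | 151 | about 168 |

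None gives 180.

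**Step 4. Sensitivity to the unstated IS rate.** If the true IS rate were 81%, the distance to the margin would be 0.14 − 0.04 = 0.10, and

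n = (1.645 + 0.842)² × (0.85 × 0.15 + 0.81 × 0.19) / 0.10² ≈ 174 assessable per group.

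A figure near 180 per group can therefore arise from a different IS rate. It would not be compatible with the bracketed 90 and 90, which follow exactly from equal rates.

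**The case against.** The strongest reply is that this is a labelling slip and not a sizing error. The inputs reproduce 90 per group and 180 in total, the design is not under-sized on its own terms, and the bracket tells a careful reader which enrolment is meant. The article also condenses a fuller protocol, and nothing shows that sites recruit from the article. All of that stands. It limits the likely practical harm, and the reading of 180 per group, with its 400 enrolled, is already excluded by the bracket.

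A second reply is that the case against the word for assessable is an inference. The IS cure rate is not stated and neither is the formula. Under Farrington–Manning or a continuity correction the number would be about 85 or about 95 instead of 81. This is fair: 81 depends on equal 85% rates and the unpooled approximation. But that combination lands exactly on the bracketed 90 after the stated 10% loss, so it is by far the likeliest source. If 90 were instead the assessable number, the 10% allowance would have been listed without being applied.

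Neither reply rescues the sentence. It states the trial's main design number with two labels that its own contents do not support, and changing only one of them would leave it wrong.

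**Conclusion.** The concern holds. The description of 180 as per group is certainly wrong: the same sentence divides 180 into 90 and 90. The description as assessable is wrong on the article's inputs: 81 per group (162 in total) must be assessable for 80.2% power, and 90 per group (180 in total) is the number to enrol after the 10% allowance. The enrolment figure is overstated by a factor of two if read per group. Read as a total, the assessable figure is overstated by 18 patients (180 against 162).

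The conclusion on 81 rests on a true cure rate of 85% in both groups and the unpooled normal approximation; exact enumeration agrees at 80.2%. The planned enrolment of 90 and 90 is not in question under those assumptions. Because this figure sets the recruitment target and underlies the primary comparison, the sentence must be corrected.

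**What to change.** Replace the result in section 2.6 with wording such as:

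*Assuming a true cure rate of 85% in both groups, 81 assessable subjects per group (162 in total) are required. Allowing for 10% non-evaluable subjects, 90 patients will be enrolled in each group (180 in total).*

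The sponsor should confirm that the IS rate was taken as 85%, and name the formula used. If either differs from the reconstruction above, the assessable number should be restated to match. The same wording should be checked wherever the sample size appears in the full protocol.

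The cost is one sentence. No extra patients are needed, and the margin, alpha, power and study procedures do not change.
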